## Abstract

**Introduction:**

Rapid coagulation assessment is crucial in emergencies, especially with acute bleeding, where timely intervention prevents shock and circulatory failure. Viscoelastic tests (VET) offer real-time insights into clot formation, fibrinolysis, and overall coagulation dynamics, often surpassing conventional lab tests. To accelerate diagnostics, hospitals use pneumatic tube systems (PTS) for blood transport. However, the effect of PTS transport on VET results remains unclear, especially with newer VET technologies and in critically ill patients, who may be more vulnerable to acceleration forces.

**Objective:**

The VETaPT (Viscoelastic Testing after Pneumatic Tube Transport) trial investigates whether PTS transport influences results of three next generation VET and platelet function testing in healthy volunteers and critically ill septic patients. It explores if acceleration during transport alters coagulation and platelet function parameters and whether septic patients exhibit increased susceptibility due to their altered coagulation profiles. A goal is to define an acceleration threshold above which PTS-related effects become clinically relevant. This threshold could allow assessment of transport suitability based on force data alone, supporting wider clinical application without repeated blood testing.

**Study design:**

This prospective, randomized clinical trial includes both healthy volunteers and critically ill septic patients. Paired blood samples are collected and randomly assigned to either manual or PTS transport, with each subject serving as their own control. Acceleration forces during PTS transport are continuously recorded using a three-axis accelerometer. Samples are analyzed using standard lab tests and following point-of-care devices: ClotPro^®^, ROTEM^®^ sigma, Multiplate^®^, and TEG6s^®^. The primary outcome is the difference in coagulation parameters between transport methods, evaluated in the context of measured acceleration forces.

**Expected results:**

This is the first study to systematically compare multiple next generation VET and platelet aggregation systems in both healthy and septic patients under controlled PTS transport conditions. It is hypothesized that PTS-induced acceleration may alter test results. Identifying a critical threshold could ensure safe, rapid blood transport without compromising diagnostic quality, potentially reducing personnel needs and expediting therapy initiation.

**Registration:**

Ethics approval was obtained from the responsible committee of the Technical University Dresden (BO-EK-12012024_1). The study is registered with the German Clinical Trials Register (DRKS00036231).

## Introduction

1

Rapid analysis of blood samples can be life-saving in time-critical emergency situations. Acute bleeding is one such scenario, requiring immediate intervention to prevent shock caused by hypoxia and hypoperfusion, which may lead to circulatory failure. The assessment of coagulation parameters plays a crucial role in guiding therapeutic decisions, such as the administration of blood products or coagulation factor treatments. To facilitate prompt intervention, these parameters must be available as quickly as possible. The development of point-of-care (POC) devices for viscoelastic testing (VET) represents a significant advantage in emergency diagnostics, enabling rapid coagulation assessment. In addition to their speed, VET devices provide valuable insights into coagulation dynamics, which are neglected in standard laboratory tests (SLT), such as INR/Quick, aPTT, platelet counts, and fibrinogen levels (1–4). Traditional tests fail to account for key cellular components of coagulation (e.g., platelets and erythrocytes), the interaction of coagulation factors, and clot resolution (fibrinolysis), all of which play critical roles in hemostasis. Under physiological conditions, clot formation and fibrinolysis are balanced, but critically ill patients may experience excessive clot breakdown (hyperfibrinolysis) or impaired clot resolution (hypofibrinolysis), leading to bleeding complications or thromboembolic events (4, 5). VET POC devices offer real-time insights into fibrinolysis, surpassing the imprecise estimations provided by SLT. By enabling faster and more targeted diagnostics, VET devices facilitate timely interventions, potentially reducing the need for blood products and improving patient outcomes (6). However, decentralized access to VET devices is not universal, making rapid transport to central VET units essential for timely results. Pneumatic tube systems (PTS) are widely used in hospitals to expedite sample transport and reduce staff workload (7). The potential impact of acceleration forces in the PTS on the VET results has been debated since the early days of these devices (8–11). However, findings remain inconsistent (12, 13), and it is unclear whether older studies apply to next generation VET devices, as manufacturers continue to develop models with increasingly diverse technical approaches (2, 14, 15). Recent developments in VET devices include platelet function analysis (16) and assessments of hypo-and hyperfibrinolysis (2). While early VET devices relied on mechanical detection of coagulation activation, newer models also incorporate acoustic measurements on the basis of the clot resonance frequency (14). This, in turn, raises new questions. Namely, whether external vibrations might influence the results of VET measurements. Indeed, Zipperlein et al. demonstrated that vibrations during helicopter transport can affect VET outcomes (17). This growing diversity complicates direct comparisons between devices and makes it difficult to predict how acceleration forces during PTS transport might affect VET results. Studies have shown that PTS transport can induce hemolysis in blood samples (18) and alter coagulation parameters (10), likely due to shear forces acting on erythrocytes and platelets. Acceleration forces are likely more relevant to shear stress than is the sustained velocity (19, 20). It is well established that mechanical forces can alter blood components even *in vivo*. For example, high shear stress in aortic valve stenosis can degrade von Willebrand factor, leading to acquired von Willebrand syndrome (21). These forces may activate coagulation factors and platelets, but the findings remain inconsistent (19, 20). Discrepancies in previous studies may arise from differences in blood sample characteristics. Blood from healthy individuals may respond differently to acceleration forces than blood from critically ill patients with altered coagulation profiles. This variation complicates comparisons between studies using healthy volunteers versus patient samples (9, 10, 22, 23). Another limitation is that most studies rely solely on manufacturer-reported transport speeds (11), while others report only maximum velocities without further analyzing the specific effect of acceleration forces during PTS transport on test parameters (8–10, 24). These approaches fail to consider the following critical issues:

Does the actual transport speed match the manufacturer’s specifications?How long is the blood sample exposed to this speed?What acceleration forces occur at the start and end of transport?Is there a correlation between the magnitude of the acceleration forces and alterations influence in POC parameters?Is the observed effect clinically meaningful, or is it merely statistically significant?

Therefore, precise quantification of the forces acting within a PTS is essential for understanding their potential impact on blood samples. This study hypothesizes that transport of blood samples via a PTS has a clinically significant impact on results obtained from next generation VET devices. This effect is expected to correlate with the magnitude of acceleration forces during transport and may differ between healthy individuals and critically ill septic patients due to sepsis-associated coagulation abnormalities.

## Methods and analysis

2

This trial protocol adheres to the SPIRIT guidance for protocols of clinical trials (25).

### Trial objectives

2.1

The Viscoelastic Testing after Pneumatic Tube Transport (VETaPT) trial study investigates whether PTS transport has a clinically significant impact on coagulation results obtained from of three next generation POC VET devices and platelet function testing in healthy volunteers and critically ill septic patients. The primary outcome is the difference in test results between manually and PTS-transported blood samples in both healthy volunteers and critically ill septic patients.

As secondary objectives, the study explores whether the magnitude of acceleration forces during PTS transport correlates with changes in coagulation parameters and whether this effect differs between healthy and septic individuals due to sepsis-associated coagulation alterations. In addition, the study aims to define a threshold of PTS-induced forces beyond which clinically relevant deviations in test results occur. The study’s area under the curve (AUC)-based method may enable the findings to be extrapolated to other PTS systems without requiring further blood sample transport and analysis. Such a threshold could help establish safe transport conditions and enable the generalization of results to other PTS systems using force measurements alone, without the need for additional blood sample testing.

### Trial design

2.2

This prospective, randomized clinical study will evaluate the effects of PTS transport on coagulation in both healthy volunteers and critically ill septic patients. Following enrolment and informed consent, blood samples will be collected from each participant. For each participant, samples for both manual and PTS transport will be drawn simultaneously and assigned randomly. An overview of the study design is provided in Figure 1. Since each participant serves as their own control, no additional control group or participant randomization is needed. Acceleration forces during PTS are continuously measured during each transport cycle via a three-axis accelerometer.

**Figure 1 fig1:**
[figure not shown]
Study Design of the VETaPT trial. Blood samples from both healthy volunteers and critically ill septic patients are collected for both manual and PTS transport and randomly assigned to a transport modality. During PTS transport, acceleration forces are continuously monitored via a three-axis accelerometer. For the investigation, blood samples will be analyzed with both standard laboratory tests and four point-of-care devices. PTS: Pneumatic tube system; POC: Point-of-care.

### Study population and recruitment

2.3

Participant selection is based on predefined inclusion criteria and is conducted entirely on a voluntary basis, with informed consent obtained before participation.

Inclusion criteria

Healthy volunteers:

≥ 18 yearsNo acute illnesses or known chronic diseases affecting coagulationNo medication intake within the last 7 daysNo known pregnancyWritten informed consent was providedCritically ill septic patients:≥ 18 yearsRequiring intensive care with a Sequential Organ Failure Assessment (SOFA) score of ≥ 9Patients were diagnosed with sepsis or septic shock within the last 48 h according to the SEPSIS-3 criteria (26).Undergoing anticoagulation therapy with unfractionated heparin (UFH), low molecular weight heparin (LMWH), or argatroban at any dosageWritten informed consent by patient or legal representativeExclusion CriteriaKnown hereditary coagulation

For recruitment, critically ill patients will be screened and allocated from the intensive care unit (ICU) of the Department of Anesthesiology an Intensive Care Medicine at the University Hospital Dresden. Healthy volunteers will be recruited via announcements at the medical faculty of the study center.

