#### Multiplate^®^

2.7.5

Multiplate^®^ (Roche Diagnostics, Basel, Switzerland) is a system for platelet aggregometry that electrically measures platelet activation after the addition of the following initiators: ADP, AA, and thrombin receptor-activating peptide 6 (TRAP). The adhesion of activated platelets to the measuring electrodes leads to a change in impedance, which is measured relative to a reference electrode. The use of multiple electrodes allows for internal quality control within each measurement.

The following laboratory, patient, and participant data will be collected as part of the study:
*Conventional laboratory parameters for hemolysis detection:*
Blood count, potassium, lactate dehydrogenase (LDH), aspartate aminotransferase (AST), haptoglobin, hemolysis index
*Conventional laboratory coagulation parameters:*
International normalized ratio (INR), activated partial thromboplastin time (aPTT), thrombin time, fibrinogen
*ClotPro^®^:*

ExTest, InTest, FibTest, tPATest, ECAtest, and RVVtest with the following parameters estimated:

Clotting Time (CT)Clotting Formation Time (CFT)Angle *α*Clot firmness after 5 min (A5)Clot firmness after 10 min (A10)Maximum Clot Firmness (MCF)Maximum Fibrinolysis (ML)Lysis time (LT)
*ROTEM^®^ sigma:*

EXTEM, INTEM, FIBTEM, APTEM – with the following parameters estimated:

Clotting Time (CT)Clotting Formation Time (CFT)Clot firmness after 5 min (A5)Clot firmness after 10 min (A10)Maximum Clot Firmness (MCF)Maximum Fibrinolysis (ML)Lysis time (LT)*TEG6s^®^*:

CK, CKH, CRT, and CFF with the following parameters estimated:Reaction Time (R)Clotting speed (K)AngleMaximum Clot Firmness (MA)Clot Stability (Lyse30)*TEG^®^ PlateletMapping* with the following parameters estimated:Maximum Clot Firmness after Kaolin with Heparinase (HKH-MA)Maximum Clot Firmness after Activator F (ActF-MA)Maximum Clot Firmness after Activator F with Arachidonic Acid (AA-MA)Maximum Clot Firmness after Activator F with ADP (ADP-MA)Percentage of ADP-inhibited platelets (ADP % Inhibition/% Aggregation)Percentage of AA-inhibited platelets (AA % Inhibition/% Aggregation)
*Multiplate^®^:*
ADPtestASPItestTRAPtest
*Demographic and disease-specific data of critically ill septic patients:*

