**Table tab3:** 

Current medication at time of blood sampling	
ACE inhibitor	Y/N
AT2 receptor blocker	Y/N
Beta blockers	Y/N
Corticoids	Y/N
Immunosuppressive medication	Y/N
Platelet inhibition	Y/N
Dual platelet inhibition	Y/N, name of drug, dose
Oral anticoagulation therapy	Y/N, name of drug, dose
Time of last intake	Date, time
Other anticoagulation drugs	Name of drug
Unfractionated heparin	Dose
Low molecular weight heparin	Dose
Other anticoagulation drug	Dose

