#### Sample size and statistical analysis

2.7.7

The primary objective of this study is to assess whether the area under the curve (AUC), as a measure of the forces exerted by the pneumatic tube system (PTS), has a clinically significant effect on coagulation analyses with the VET. The parameter used for sample size calculation is the clotting time (CT), a test result of viscoelastic testing. The primary endpoint for the sample size calculation is the binary outcome of a clinically significant change in CT. Clinical significance is defined on the basis of established treatment algorithms used in routine clinical practice (2). In these treatment algorithms, a CT change of ≥20 s in the ClotPro^®^ ExTest significantly influences therapeutic decisions and is thus considered clinically relevant. To enhance the level of safety, in this study a clinically significant difference was defined as a change in CT of ≥10 s between manual transport and PTS transport. A logistic regression model is employed for the sample size calculation, with the binary outcome of a clinically significant change as the dependent variable. We plan to perform the analysis after the completion of the study via logistic regression as well. The independent variables will be the AUC in both cohort (healthy participants vs. critically ill septic patients). Owing to the lack of prior data for sample size planning via ClotPro^®^, estimates will be derived from published data on ROTEM^®^. Given the similar underlying principles of both devices, these data can reasonably be applied for sample size estimation.

The sample size calculation is based on estimating the probability of the primary endpoint under two conditions (H_0_ and H_1_). Since direct probability estimates for H_0_ and H_1_ are unavailable, literature data for CT are used:

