## Discussion

3

Previous findings on the impact of PTS commonly used in hospitals on VET results are inconsistent (12, 13) and may not be applicable to next generation VET devices (2, 14, 16). This study aims not only to determine whether PTS exerts a clinically significant influence on VET results but also to identify factors contributing to potential alterations. The following aspects are considered:

*VET-related factors*: a comparison of next generation VET devices;*PTS-related factors*: assessed by continuously quantifying acceleration forces;*Patient-related factors*: analyzed by comparing healthy volunteers with sepsis patients;

This study represents the first to allow such a differentiated approach within a single study design. By utilizing this design, future research can facilitate the transferability of findings to other PTS systems by measuring the acceleration forces acting on transported samples, independent of manufacturer-reported transport speeds. Furthermore, the comparison of healthy volunteers with sepsis patients in this study aims to provide insights into whether pathological coagulation activation in sepsis patients alters susceptibility to acceleration forces. These findings may help explain the discrepancies reported in previous studies, which focused on either healthy individuals or patient cohorts (9, 10, 22, 23). The sub-experiment in this study employing a vibration exciter enables differentiation between the effects of absolute acceleration magnitudes and continuous exposure to acceleration forces on the VET results. These insights could form the basis for further investigations into coagulation activation in extracorporeal circulation settings, where both shear stress and flow acceleration occur.

A study-related limitation is the lack of blinding of investigators during the initiation of VET measurements. However, as VET measurements follow a standardized protocol, the impact of this limitation is considered minimal. Another limitation is the inability to assess intra-device measurement variability, i.e., the precision of the VET devices. Due to the necessity in this study of multiple measurements under both transport conditions and the maximum sample capacity of the devices, additional measurements to evaluate device precision could not be performed within the predefined time frame after blood collection.

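### All septic patients are anticoagulated and all volunteers are medication-free by eligibility, so a cohort difference in the transport effect cannot be attributed to sepsis

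*Protocol article*

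**What the plan says.** Eligibility (Protocol article, section 2.3, Study population and recruitment): a septic patient qualifies only if "Undergoing anticoagulation therapy with unfractionated heparin (UFH), low molecular weight heparin (LMWH), or argatroban at any" dosage. A healthy volunteer qualifies only without any medication in the preceding 7 days.

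Attribution of a cohort difference:
- Introduction: the transport effect "may differ between healthy individuals and critically ill septic patients due to sepsis-associated coagulation abnormalities".
- Section 2.1, Trial objectives (secondary objectives): the study explores "whether this effect differs between healthy and septic individuals due to sepsis-associated coagulation alterations".
- Discussion: the cohort comparison "aims to provide insights into whether pathological coagulation activation in sepsis patients alters susceptibility to acceleration forces".

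Analysis (section 2.7.7): a logistic regression for a clinically relevant change in clotting time (CT), in which "The independent variables will be the AUC in both cohort (healthy participants vs. critically ill septic patients"). The planned size is 92, split into 46 per cohort.

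The medication table for septic patients records the dose of unfractionated heparin, "Low molecular weight heparin" and other anticoagulants. The limitations in the Discussion cover the lack of blinding and device precision, but not the difference in anticoagulant exposure.

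**The concern.** The cohorts differ in two ways that are both fixed by eligibility: sepsis and anticoagulation. The outcomes are coagulation measurements, with a change in CT as the sample-size endpoint, and only one cohort's blood carries an anticoagulant during transport. If the PTS effect is larger or smaller in patients, the drug is as good an explanation as the disease. If no difference appears, a sepsis effect may have been offset by the drug.

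The mechanistic part of the secondary objective is at stake. The Discussion also hopes that the comparison will help explain why earlier studies in volunteers and in patients disagreed. A publication that credits sepsis with the difference would claim something this design cannot show.

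**Working it through.** **Inputs.** Anticoagulated share of the septic cohort: 100% (section 2.3). Anticoagulated share of the healthy cohort: 0% (section 2.3). Cohort size: 92/2 = 46 (section 2.7.7).

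**What pairing does.** Write participant i's manual result as m_i and the PTS result as m_i + d_i. The paired difference is d_i. The baseline level m_i, including any drug or disease effect on it, cancels. The response d_i does not cancel, and it may depend on sepsis, on the anticoagulant, or on both. The cohort contrast compares d_i between cohorts.

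**What the cohort contrast identifies.** Let S = 1 for septic and A = 1 for anticoagulated. A model that allows both to modify the effect of acceleration is, on the logit scale or for the CT difference itself:

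b0 + b1·AUC + b2·S + b3·A + b4·AUC·S + b5·AUC·A

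Eligibility forces A = S for everyone, so this collapses to:

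b0 + b1·AUC + (b2 + b3)·S + (b4 + b5)·AUC·S

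Only the sums b2 + b3 and b4 + b5 can be estimated. As a check on the design matrix with 46 septic and 46 healthy participants:
- columns [1, S, A]: rank 2 of 3;
- columns [1, AUC, S, A, AUC·S, AUC·A]: rank 4 of 6.

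The correlation between S and A is exactly 1. Neither rank depends on N, so the result is the same for 83 pairs, 92 pairs or any other number.

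**What this means for interpretation.** An interaction of size 1 (arbitrary units) fits b4 = 1, b5 = 0 (all sepsis) and b4 = 0, b5 = 1 (all drug) equally well. An interaction of 0 fits b4 = 1, b5 = −1 (a sepsis effect masked by the drug).

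**Could the recorded doses rescue the attribution?** Every septic patient is exposed, so a within-septic dose analysis must extrapolate to zero dose. It is also small: 46 patients, or 46 × 0.9 = 41.4 (about 41) after the assumed 10% dropout. With two-sided alpha 0.05 and 80% power, the smallest detectable correlation is r = tanh[(1.960 + 0.842)/√(n − 3)]:
- n = 46: tanh(2.802/√43) = tanh(0.427) = 0.40;
- n = 41: tanh(2.802/√38) = tanh(0.455) = 0.43.

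This is before any covariate is added. A real dose relation weaker than about 0.4 would probably be missed, so a flat result would not show that the drug is irrelevant.

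**The case against.** Much of the case on the other side stands.

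- **The reach is narrow.** Section 2.1 defines the primary outcome as the within-person difference between manual and PTS transport. A reader might infer that this comparison is confounded too. It is not, because both samples come from the same person under the same medication. Section 2.5 also gives a practical reason for two cohorts, namely whether volunteer findings carry over to such patients. That remains answerable for the patients enrolled.
- **The wording is tentative.** The text gives a hypothesis and an exploratory aim, so it would be wrong to say that the plan already states a mechanistic conclusion. The abstract's objective refers only to the patients' altered coagulation profiles, which does not exclude drug effects. The causal clauses in the Introduction and section 2.1 do name sepsis, however, and the Discussion does the same.
- **The model may be fuller than the article shows.** A reader might infer that cohort is the only covariate besides AUC. The article does not say so, and its allowance for correlation with other predictors (R² = 0.36) leaves room for more. Missing adjustment terms are therefore not the point. No analysis plan, seen or unseen, could undo the aliasing by adjustment.
- **An age gap is not documented.** Recruitment through the medical faculty might suggest younger volunteers, but the article gives no upper age limit or expected ages.
- **Heparinase channels are collected.** TEG6s includes CKH and "Maximum Clot Firmness after Kaolin with Heparinase (HKH-MA"). These help only in part. Heparinase is directed at heparin, whereas argatroban is also permitted. It acts in the assay, after transport has already happened. It also does not touch the ClotPro ExTest CT on which the endpoint rests. HEPTEM is described for ROTEM sigma but is not among the ROTEM tests listed for collection.

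**Conclusion.** The point holds for the attribution and for nothing wider. Sepsis and anticoagulation are completely aliased in the cohort contrast (46 of 46 against 0 of 46), at any sample size. A difference in the PTS or AUC effect can be reported as a difference between anticoagulated septic ICU patients and medication-free volunteers, but not as an effect of sepsis. The conclusion rests only on both eligibility criteria being applied as written. How far anticoagulation changes the response to transport cannot be judged from the article, so the size and direction of any resulting error are unknown.

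A reader might also infer that a flat relation between anticoagulant dose and transport effect would justify a sepsis-specific statement. It would not: all patients are exposed, a group of 41 to 46 could easily miss a real relation, and failing to detect one is not evidence that none exists.

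**What to change.** - In the Introduction, section 2.1 and the Discussion, describe the contrast as anticoagulated critically ill septic patients versus medication-free healthy volunteers. Delete the clauses that ascribe a difference to sepsis-associated coagulation changes, and reword the Discussion sentence on pathological coagulation activation in the same way.
- Add to the limitations that sepsis and anticoagulation cannot be separated in the cohort comparison. State that no sepsis-specific conclusion will be drawn from it.
- Optionally, report a small within-septic analysis of the transport effect by recorded anticoagulant class or dose, together with the TEG6s CK and CKH channels. Label it exploratory, and state beforehand that a null dose relation will not be used to support a sepsis-specific claim.

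Eligibility, sample size and data collection stay as they are. The cost is a few sentences and a more modest claim, and any within-septic estimates will be imprecise.

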H₀ (Null Hypothesis): The probability of a clinically relevant CT change when the AUC is at its mean value, i.e., manual transport, where no significant effect is expected. The probability of a clinically relevant CT change due to manual transport is considered very low. On the basis of Martin et al. (10), this probability is estimated at 0.045.H₁ (Alternative Hypothesis): The probability of a clinically relevant CT change when the AUC is at its mean plus one standard deviation, i.e., PTS transport, where an effect is expected. The probability of a clinically relevant CT change due to increased AUC in PTS transport can be inferred from the method established by Streichert et al. (28). On the basis of the mean difference and standard deviation of CT changes between transport methods in Martin et al. (10), this probability is estimated at 0.21.

Sample size calculation was performed via G-Power 3.1 (29) with the following parameters: significance level (*α*) = 0.05; power (1-*β*) = 0.8; two-sided test; R^2^ other X = 0.36; Wald’s Z test. The total required sample size was determined to be N = 83 paired comparisons (manual vs. PTS transport). Considering potential dropouts due to sampling errors, withdrawal of consent, or failures in point-of-care testing, a dropout rate of 10% is assumed, increasing the total required sample size to 92. The participants will be equally distributed between the two study groups, resulting in 46 cases per group (e.g., healthy volunteers and critically ill septic patients).

Baseline comparisons between the two cohorts will be conducted via t tests for normally distributed data and the Wilcoxon test when normality is violated. Normality will be assessed via the Shapiro–Wilk test. A *p* value ≤ 0.05 was considered statistically significant. All the statistical analyses will be performed via MATLAB software (The MathWorks Inc., 2024).

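### Healthy-volunteer recruitment does not secure age and sex comparability with the septic cohort, so a between-cohort difference in the transport effect cannot be attributed to sepsis

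*Protocol article*

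**What the plan says.** Section 2.3 of the protocol article sets out both cohorts. Healthy volunteers must be at least 18, free of acute illness and of known chronic disease affecting coagulation, not known to be pregnant, and without any medication for 7 days. Their source is given in one sentence: "Healthy volunteers will be recruited via announcements at the medical faculty of the study center". Septic patients must also be at least 18, need intensive care with a SOFA score of 9 or more, and be receiving anticoagulation. No upper age limit, age strata, sex quota or matching is stated for either cohort.

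Section 2.1 makes the cohort comparison a secondary objective and names a cause: the study asks "whether this effect differs between healthy and septic individuals due to sepsis-associated coagulation alterations". The Discussion repeats the aim as learning "whether pathological coagulation activation in sepsis patients alters susceptibility to acceleration forces".

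On control of confounding, section 2.2 says: "Since each participant serves as their own control, no additional control group or participant randomization is needed". Section 2.7.7 gives the model: "The independent variables will be the AUC in both cohort (healthy participants vs. critically ill septic patients"). It adds: "Baseline comparisons between the two cohorts will be conducted via t tests for normally distributed data and the Wilcoxon test when normality is violated". Date of birth and gender are on the data lists for both cohorts, and the article states no use for either in the cohort comparison.

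**The concern.** Each participant's two samples differ only in how they travelled, so stable characteristics such as age and sex cancel from the manual-versus-tube contrast. The secondary question is different. It compares the size of that within-person change between two groups that were not randomised. Anything that alters how strongly a sample responds to transport, and that differs between the groups, remains in the comparison. Being one's own control gives no protection there.

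Volunteers come from one announcement channel and patients from an intensive care unit, and nothing in the plan makes their age and sex distributions alike. If the septic samples changed more under transport, the plan as written would lead the authors to ascribe this to sepsis. The same result could arise from age, sex, or both. The Discussion also hopes to explain why earlier studies in healthy people and in patients disagreed, and that explanation would carry the same ambiguity.

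**Working it through.** **Plan's own figure.** The article gives no expected age or sex mix for either cohort, so there is nothing to reproduce on this point. The planned 83 evaluable pairs serve below only as a base for scale.

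**Where age enters.** Let D be the paired change in clotting time. Suppose D depends on AUC, on cohort (effect b), and on age with slope g seconds per year. The unadjusted cohort difference at equal AUC is then

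b + g × (mean age septic − mean age healthy).

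The article fixes neither g nor the age gap, and g may be zero. For scale, section 2.7.7 states that "a clinically significant difference was defined as a change in CT of ≥10 s between manual transport and PTS transport". The slope at which age alone would shift the cohort difference by 10 s is 10 divided by the gap: 1.0 s per year for a gap of 10 years, 0.5 for 20, 0.29 for 35 and 0.25 for 40. No value of g can be taken from the documents.

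**Can later adjustment separate age from cohort?** All means and SDs below are assumptions. With two equal cohorts and a linear age term:

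- between-cohort variance of age = (gap / 2)²
- within-cohort variance = (SD₁² + SD₂²) / 2
- R² of cohort on age = between / (between + within)
- variance inflation for the cohort term = 1 / (1 − R²)
- equivalent number of pairs = 83 × (1 − R²)

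| Assumed mean age, healthy vs septic (SDs) | Between | Within | R² | Variance inflation | Equivalent pairs of 83 |
|---|---|---|---|---|---|
| 50 vs 60 (15, 15) | 25 | 225 | 0.10 | 1.1 | 75 |
| 40 vs 60 (12, 15) | 100 | 184.5 | 0.35 | 1.5 | 54 |
| 30 vs 65 (8, 13) | 306.25 | 116.5 | 0.72 | 3.6 | 23 |
| 25 vs 65 (4, 13) | 400 | 92.5 | 0.81 | 5.3 | 16 |

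The last row, worked through: 400 / (400 + 92.5) = 0.81, and 83 × (1 − 0.81218) = 15.6.

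This is a linear-model approximation. In the lower rows the adjusted estimate also relies on extrapolating the age slope across a range where the cohorts barely meet.

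**Room in the binary model.** Section 2.7.7 assumes event probabilities of 0.045 at mean AUC and 0.21 at one SD above. If all 83 transports sat at one or the other value, events would number 83 × 0.045 = 3.7 or 83 × 0.21 = 17.4. That is thin support for a logistic model with AUC, cohort, age and sex. The continuous paired difference carries more information for this comparison.

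**The case against.** Several counter-arguments have force.

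- **No ages are given.** A reader might infer that the contrast simply is one of young against old. The documents do not support that as fact. Both cohorts have the same lower limit and no upper one, and a faculty has staff as well as students. The table shows how far the answer moves with the ages assumed. The point is that comparability is not secured, not that it is known to fail.
- **No evidence of effect modification.** Nothing in the documents says that age or sex changes susceptibility to transport forces. This stands, so the bias cannot be sized. The design could nevertheless not tell such modification from sepsis.
- **The primary contrast is safe.** A reader might infer that the main result is compromised. It is not, because manual versus tube transport is compared within participant, with samples assigned at random.
- **The baseline tests are only descriptive.** A reader might infer that the plan relies on them to repair imbalance. The article makes no such claim.
- **Adjustment may be in an analysis plan not shown.** This is fair, and the missing age term would not be a fault on its own. Recruitment source and eligibility, however, belong to the protocol, and no later analysis can create overlap that recruitment did not provide.
- **The purpose is partly pragmatic.** Section 2.5 asks whether findings in healthy volunteers carry over to septic patients. For that question age is part of the population difference, and an unadjusted contrast is reasonable. The attribution to sepsis in section 2.1 goes further.
- **Matching leaves other differences.** Anticoagulation is required in one cohort and all medication is barred in the other, and illness severity separates them completely. This stands in full, and it is why the attribution itself must be limited.

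**Conclusion.** The concern holds for the secondary between-cohort comparison only. The volunteer source and criteria do not ensure age and sex comparability, the stated model has no term for either, and the objective nevertheless names sepsis as the cause of a difference.

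The practical size depends on ages that the documents do not give. If the cohorts' mean ages are about 10 years apart with wide spread, later adjustment costs about a tenth of the information on cohort. If they are 35 to 40 years apart with narrow spread among volunteers, it costs roughly 72 to 81 per cent. These figures assume equal cohorts and a linear age effect. Whether any bias exists depends on an effect of age or sex on the paired change, which is unknown. Even with full balance on both, the design would support a statement about anticoagulated septic ICU patients against healthy volunteers, and not one about sepsis alone.

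**What to change.** 1. **Recruitment (section 2.3).** Announce beyond the medical faculty and frequency-match the same 46 volunteers to the age-band and sex mix expected in the septic cohort, for example 18–39, 40–59 and 60 or over, by sex. Set the target mix in advance, so that volunteer enrolment need not wait for patients to accrue.
2. **Analysis (section 2.7.7).** Include age and sex, already recorded, in the between-cohort comparison, for example in a linear model for the continuous paired difference in clotting time. Show the age distributions by cohort. If overlap is poor, say so and do not rely on the adjusted estimate.
3. **Interpretation (section 2.1 and Discussion).** Describe the contrast as anticoagulated septic ICU patients versus healthy volunteers. Drop the attribution to sepsis alone, because anticoagulation and illness severity remain confounded with cohort after matching.

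The cost is a wording change, a wider announcement, and somewhat slower volunteer recruitment within the 9-month phase, since older people without any recent medication are probably harder to find. No extra participants or tests are needed. The medication criterion can stay as it is: relaxing it would widen the pool but make the reference group less uniform, and this point does not depend on it.
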